## Methods/Design

### Approach to research questions

The primary outcomes of this trial are the assessment of cardiovascular (changes in , plasma albumin content and plasma volume) and intramuscular (selected genes and proteins involved in cellular adaptive processes) training-induced adaptations, and whether protein co-ingestion (immediate or overnight) improves the magnitude of these adaptations. In accordance, two phases of testing will be conducted.

Phase I will be addressed by evaluating a carbohydrate-protein mixture against an energy-matched carbohydrate control to examine the influence of post-exercise protein intake in enhancing endurance training adaptations. Participants in Phase I will be randomly allocated to a group receiving an isocaloric carbohydrate supplement or a group receiving a carbohydrate-protein supplement, in a randomized investigator-participant double-blind manner, whereby the chief investigator ([name]) and participants will be blinded from the trial allocation. The acute post-exercise phase is important when considering the metabolic priority for recovery to be initiated [3, 21] and the potentiated sensitivity to nutritional interventions during this period [22]. It has been established that glycogen resynthesis and amino acid uptake rates are augmented following an exercise bout, and that the ingestion of carbohydrate and protein stimulate this process [6, 23–25]. This has subsequently prompted large numbers of studies to investigate the role of combined carbohydrate-protein ingestion in restoring glycogen stores, potential attenuation of decrements of skeletal muscle functional integrity and subsequent exercise performance [12, 26]. It is now generally accepted that incorporating protein into a post-exercise feeding regimen is a viable strategy to enhance recovery, mainly through observations in acute based studies [7, 8, 21, 27–33]. Yet, the effects of protein ingestion are more likely to be realized beyond the acute recovery phase, given that upregulation of endurance exercise-specific gene expression peaks between 10 and 24 hours following an exercise bout, and may surpass 96 hours for muscular recovery and adaptive remodeling to occur, suggesting that repeated bouts of exercise are required to detect worthwhile training adaptations [3, 34].

Given that the target population will be physically untrained and subjected to running-based aerobic exercise training, and that reversal of these training-induced adaptations are relatively slow in such individuals [35], the study will adopt a randomized parallel group design in each phase with a relatively larger cohort of participants to account for inter-individual variability. The duration of the training period will be six weeks. This duration was deemed adequate based on previous literature, which demonstrated that approximately four weeks (total number of sessions was between 20 and 22 during the entire protocol) elicits changes in  of 6 to 14%, oxidative enzyme activities of 35 to 50% and mitochondrial protein content of 50 to 100% in untrained and moderately trained individuals [11, 36, 37].

Phase II of testing will examine the influence of protein timing upon mediating the adaptive response to endurance exercise. Participants will be randomly assigned to a group receiving the same carbohydrate-protein mixture in Phase I, but with one group ingesting the supplement immediately post-exercise, while the second group supplementation will take place during overnight recovery in a double-blinded manner. The interaction between exercise and protein ingestion on mitochondrial protein synthesis may lie outside the acute recovery phase (over eight hours post-exercise) and under circumstances of rested mitochondrial turnover rates [8, 19]. Moreover, the provision of dietary protein prior to sleep was shown to be an effective nutritional strategy to further augment muscle protein synthesis during overnight recovery [38]. Coupled with the fact that exogenous amino acids stimulate mitochondrial synthetic response in the rested state [18], protein intake during overnight recovery may increase the adaptive response to endurance training relative to immediate feeding. Therefore, comparisons between immediate versus overnight protein ingestion (Phase II) are warranted to provide an insight into the molecular and transcriptomic responses that could extend the knowledge regarding the relationship of nutrient-exercise stimuli to mitochondria biogenesis.

It has also been established that rapid hyperaminoacidemia (particularly leucine) is required to maximize muscle protein synthetic response; however, this response is returned to baseline approximately three hours after a single bolus of ingested protein within the recommended quantities (approximately 0.3 to 0.4 grams per kilogram of body mass; g · kg BM^−1^) for maximal muscle protein synthesis [39–41]. Therefore, it may be postulated that a second bolus would be advantageous in inducing hyperaminoacidemia and would supply sufficient amounts of leucine into circulation to prompt the ‘leucine trigger’ [40, 42, 43], consequently maximizing muscle protein synthesis during post-exercise overnight recovery.

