### Experimental design

The proposed project involves two distinct phases of testing, each contrasting two nutritional interventions in a randomized investigator-participant double-blind parallel group design. The independent variable will be the precise nutritional intervention ingested following exercise in Phase I, while timing of ingestion will be the independent variable in Phase II. Specifically, those participants recruited for Phase I (n =32, approximately) of testing will receive a supplement containing carbohydrate (sucrose) plus protein (whey protein hydrolysate) at an ingestion rate of 0.4 and 0.4 g · kg BM^−1^ respectively. The second group will be a control group, whereby an ingestion of an isocaloric carbohydrate supplements will be assigned (0.8 g · kg BM^−1^). The two nutritional interventions provided in Phase II (n =32, approximately) will be identical (0.4 g · kg BM^−1^ carbohydrate +0.4 g · kg BM^−1^ whey protein hydrolysate), while the timing of intake will be manipulated. A group will ingest the carbohydrate-protein supplement immediately post-exercise and one hour later, while the overnight recovery group will receive the supplements one hour prior to sleep, and at 02:00, as an overnight nutritional intervention. The nutritional information for the supplements is provided in Table 1.

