### Training intervention

Exercise sessions performed in the baseline testing week will last for 30 minutes and thereafter the duration of sessions will progressively increase to 40, 50 and 60 minutes in week one, weeks two to three, and weeks four to six, respectively. Prior to any exercise session, a five-minute warm-up at 60%  will be superimposed, followed by treadmill running at a speed corresponding to 70%  for the durations indicated above. The target %  will be attained by providing participants with their relative speeds at any given intensity during the training intervention, which will be determined by linear regression (Excel 2010, Microsoft, Redmond, Washington, United States) during the first baseline visit. During the midpoint (training week three), the speed will be increased to elicit 75% . Only water consumption will be permitted during exercise sessions, which will be consumed *ad libitum*. Upon cessation of each exercise session in Phase I, a post-exercise nutritional supplement will be ingested immediately, while a second bolus will then be consumed one hour after the end of exercise. In relation to Phase II of testing, one group will ingest a post-exercise nutritional supplement in a similar manner to Phase I, while the other group will ingest an identical supplement one hour prior to sleep and at 02:00. During the nutritional provision periods, participants will be instructed to consume only water to avoid any confounding results relating the outcome variables of the study. Once every fortnight, participants will report to the laboratory to provide the nutritional supplements for the subsequent two-week training block, with a total of three scheduled meetings throughout the training intervention. This visit is also to confirm the adherence of participants to the prescribed training and supplementation procedures.

Although several risk factors will be screened before participants take part in exercise, the prescribed physical exercise may increase the risk of certain adverse events (such as myocardial infarction, musculoskeletal injuries and so on). Nevertheless, the prescribed endurance training will be conducted in a gymnasium under supervision of trainers who are familiar with first aid procedures, and the occurrence of any adverse events related to the study will be reported.

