### Submaximal and maximal oxygen uptake measurements

Running economy (· km^−1^) and () measurements will be assessed for participants during the first laboratory visit during baseline and follow-up testing [49]. These tests initially require participants to run on a motorized treadmill (Ergo ELG70, Woodway, Weil am Rhein, Germany). The protocol involves a standardized five-minute warm-up that consists of jogging at a speed of 7.5 km · h^−1^, followed by a running economy test. This requires participants to run at various submaximal speeds with increments of 1 km · h^−1^ to enable a minimum of four different running speeds (8 to 11 km · h^−1^). Each running speed will consist of three-minute stages, during which expired gas, heart rate (HR) and ratings of perceived exertion (RPE) will be recorded at the final minute of each stage. Expired gas samples, HR and RPE will be obtained via the Douglas bag method, short range telemetry (Polar FT2, Kempele, Finland) and Borg’s scale (range of the scale: 6 to 20) [50], respectively. Approximately 20 minutes following the submaximal test, a run time to volitional exhaustion will be initiated to determine relative  values for participants, which is described in further detail elsewhere [47]. The criteria of the British Association of Sport and Exercise Sciences for establishing  in adult subjects will be used to ensure the attainment of 
[51]. These will include the achievement of a maximal HR within 10 beats · min^−1^ from the predicted HR maximum for participants (220 beats · min^−1^ − age), respiratory exchange ratio (RER) values of 1.1 or greater and subjective indication of volitional exhaustion on the RPE scale. The data acquired from these tests will subsequently be used to calculate the treadmill speeds required by the trial procedures (speeds that elicit 60, 70 and 75% ) by linear regression (Excel 2010, Microsoft, Redmond, Washington, United States).

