During prescribed training days, participants will be required not to perform any other structured exercise session and will be instructed to ingest a meal (breakfast or lunch, depending on the time of day) approximately two hours prior to any session, and thereafter abstain from any caloric intake prior to the commencement of the training session. Participants will also be instructed not to consume any calories outside the scope of the prescribed supplements during the designated supplement provision periods (either two hours immediately post-exercise or one hour prior to sleep and throughout the overnight period, depending on the phase of testing). A checklist will be included in Phase I and Phase II of testing to confirm supplement intake, time of ingestion and avoidance of any caloric intake outside the scope of the prescribed supplements. This is aimed to ensure adherence to the nutritional intervention intake and timing throughout the training period.

In an attempt to accurately monitor training and ultimately standardize the training load between treatments *in situ*, an exercise diary will be provided to each participant. Participants will complete the relevant information relating to the exercise session (time of day the training session was started, total duration of session) on any of the training days, which will then be verified by an electronic monitoring system that requires participants to use a key card to enter and leave the gymnasium. Once the study is completed, the exercise logs will be collected and cross-examined with the electronic monitoring system to verify adherence for each exercise session attendance, for each date and duration.

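### Phase II is called investigator-participant double-blind, but its arms differ only in when an identical drink is taken, so participants cannot be blind to their arm

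*Protocol article*

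**What the plan says.** The Experimental design section describes two phases, "each contrasting two nutritional interventions in a randomized investigator-participant double-blind parallel group design"; the abstract says the same. Approach to research questions applies the claim to Phase II in particular, with the overnight arm supplemented "while the second group supplementation will take place during overnight recovery in a double-blinded manner". For Phase I that section explains the term: the chief investigator is blinded, and "participants will be blinded from the trial allocation".

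On what the arms receive, Experimental design states: "The two nutritional interventions provided in Phase II (n =32, approximately) will be identical". Timing is named there as the independent variable. One arm drinks straight after exercise and again an hour later, "while the overnight recovery group will receive the supplements one hour prior to sleep, and at 02:00". Training intervention repeats this schedule and allows only water during the provision periods. Table 1 lists two products, both at 320 kcal, and no non-caloric one.

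On records, Standardization of lifestyle says: "A checklist will be included in Phase I and Phase II of testing to confirm supplement intake, time of ingestion". Training intervention sets fortnightly laboratory visits and adds: "This visit is also to confirm the adherence of participants to the prescribed training and supplementation procedures".

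On outcomes, Approach to research questions counts maximal oxygen uptake among the primary cardiovascular outcomes, beside the intramuscular markers. To measure it, "a run time to volitional exhaustion will be initiated".

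**The concern.** In Phase I the allocation lies in the contents of the drink, which coded sachets can hide. In Phase II the allocation is the time of drinking, which coding cannot hide from the person who drinks. The article therefore states a bias safeguard that its own schedule rules out for participants.

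What is at stake is mainly the oxygen-uptake result. A test that ends when the participant chooses to stop depends on motivation and on encouragement from the tester. If participants know their arm, or if the tester has seen the ingestion times, part of a difference between arms could reflect expectation. Readers told that the comparison was double-blind would not allow for that.

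**Working it through.** No arithmetic decides this point; the passages are set side by side.

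1. **The claim.** The abstract, Approach to research questions and Experimental design all describe Phase II as double-blind. The abstract and Experimental design name both investigator and participant.

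2. **What differs between the Phase II arms.** Product: nothing. Timing: everything.

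| | Immediate arm | Overnight arm |
|---|---|---|
| First drink | immediately after exercise | one hour before sleep |
| Second drink | one hour after exercise | 02:00 |
| Drink described at the other arm's times | none | none |

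3. **Can masking be read into the text?** A participant could stay blind if every participant drank at all four times and did not know which pair was active. The article gives each arm two drinking times only, and Table 1 contains no product that could serve as a dummy. No other masking device is described.

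4. **Who knows the arm?** Every participant does, from the first supplement: approximately 32 of 32 planned for Phase II. The Participants section says the information sheet sets out the study aims, so participants may also know what is being compared. Among staff, anyone who reads the checklist or confirms supplementation adherence at a fortnightly visit can learn the arm. The article does not say who that is.

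5. **Which outcomes are exposed?**
   - *Maximal oxygen uptake.* The section on submaximal and maximal oxygen uptake lists three criteria: heart rate within 10 beats per minute of predicted maximum, a respiratory exchange ratio of at least 1.1, and subjective exhaustion on the exertion scale. The first two guard against clearly submaximal tests. They set a floor and do not fix the point at which a participant stops, so protection is partial.
   - *Intramuscular markers.* These come from PCR, Western blotting and a citrate synthase assay (Muscle biopsy sampling). The supervisor who takes the biopsies is said not to know the participants' code numbers (randomization paragraph under Exclusion criteria).
   - *Plasma volume and albumin.* These derive from laboratory measurements of hemoglobin, hematocrit and albumin (Blood sampling).

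   The Background hypothesis for Phase II concerns the intramuscular markers, so the outcomes that carry it are less exposed to expectation than the exercise test.

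6. **What the contrast estimates.** Only the overnight arm has a 02:00 intake, and no matched night-time procedure is described for the other arm. The contrast is therefore between two whole strategies.

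**The case against.** The strongest reply is that the mislabel does little harm. The Phase II hypothesis rests on assays that cannot respond to encouragement, the biopsy taker is kept from the codes, both arms receive the same active product, and two of the three criteria for a valid maximal test are physiological. Most of this stands and limits the point. It does not remove it, because oxygen uptake is still listed as a primary outcome and the double-blind statement is still untrue of participants.

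A second reply is that a condensed article may omit a masking device found in the full protocol. That would excuse silence. Here the article gives a complete intake schedule and product list, and together these reveal the arm.

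A reader might also infer more than the documents support:

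- *That the chief investigator and the exercise testers are certainly unblinded.* No one is named as reading the checklist or confirming adherence, so this is a risk and not a stated fact.
- *That broken sleep makes the comparison invalid.* The 02:00 intake is presented as part of an overnight nutritional intervention, and testing that package is a legitimate choice. Sleep interruption is itself inferred from the clock time. The point bears on interpretation only.
- *That ordinary meals confound timing because each arm eats freely outside its own window.* Standardization of lifestyle asks participants to keep energy intake and habits constant and collects three three-day dietary records during training. It also ties the no-calorie window to the phase of testing, so windows specific to each arm are partly a matter of interpretation.
- *That a double-dummy is needed.* It would raise the drinks from two to four on each occasion and require a matched non-caloric version of a drink with 40 g/l of protein. The article does not show that this can be made.

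**Conclusion.** The point holds in this form: Phase II is stated to be blind to participants and, as described, cannot be. This affects all of the approximately 32 participants, and staff blinding is at risk wherever ingestion times are seen. The consequence falls mainly on the maximal oxygen-uptake result; the muscle and plasma assays are less exposed. The direction and size of any bias cannot be derived from the document.

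The conclusion rests on two readings: that the printed schedule is complete, so that no dummy is taken, and that participants follow it and so know when they drink. It does not depend on the checklist reaching any particular member of staff.

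The statement should be corrected before Phase II starts, because it misdescribes a central safeguard. Nothing here bears on the blinding of Phase I or on which feeding schedule is preferable.

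**What to change.** Trial status says that Phase II recruitment is still to come, so the following can be settled before any participant is affected.

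1. In the abstract, Approach to research questions and Experimental design, restrict the double-blind description to Phase I. Describe Phase II as participant-unblinded with blinded outcome assessment.
2. State that in Phase II the exercise testers, the biopsy taker and the laboratory analysts remain blind to arm.
3. Keep the ingestion-time checklist and the fortnightly adherence review away from whoever runs the exercise tests until follow-up is complete, and ask participants not to discuss their schedule with the testers.
4. Report the Phase II oxygen-uptake result as participant-unblinded, together with how many tests in each arm met the heart-rate and respiratory exchange ratio criteria.
5. State that a difference between arms will be interpreted as the effect of the overnight strategy as a whole, including the 02:00 intake, and not of protein timing alone.

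The cost is a less favourable design label and minor routing of forms. If the review of adherence and the exercise tests are at present planned for the same person, one of the two tasks has to be reassigned. No change to the supplements or their schedule is needed.

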### Participants

A total of 32 research participants will be recruited for each phase from the local community via public advertisement (including online posts and distribution of flyers) and personal communication. Upon contacting the chief investigator ([name]), participants will be provided with a participant information sheet detailing the study aims and requirements. Participants who express their interest will be scheduled for an initial meeting to assess their eligibility and provide further details regarding the study requirements. An informed consent form will be obtained from individuals who agree to participate following the briefing, indicating their full understanding of the study and their protected rights for confidentiality and withdrawal from the study. Thereafter, a medical health questionnaire will be undertaken by each participant to ensure the absence of any physical, hematologic, metabolic or any other health conditions. If any of the factors above are present, the volunteer will be deemed unfit to participate in the study and will consequently be excluded from taking part. Further health screening and a patient-specific direction for the use of anesthetic will be completed and sent to a medical practitioner, who will respond to confirm the absence of any contraindications prior to any local anesthesia administration.

The protocol described herein was reviewed and approved by the National Health Service (NHS) South West 3 Research Ethics Committee (approval number: 13/SW/0239). The project was subsequently registered as a controlled trial (Current Controlled Trials registration number: ISRCTN27312291). The individuals who participate in Phase I of testing will not be eligible to take part in Phase II.

### Inclusion criteria

The inclusion criteria for this study are as follows:Both male and female volunteers.Aged between 18 and 48 years.Individuals free from cardiovascular, metabolic or joint disease as determined by a standard health questionnaire.No engagement in structured physical activity for more than two hours per week during the last two years.Nonsmoker.

